**Research Plan**

**1. Background**

According to the results of the 8th National Physical Fitness and Health Survey published by the Ministry of Education in 2021, the rate of students aged 6 to 22 years meeting physical health standards in 2019 was only 23.8%. Physical education classes are the primary channel for promoting student health. However, traditional physical education teaching in China has had limited impact on the overall health level of students. To address the continuous decline in students' physical health over the past 30 years, the high obesity rate, and a series of physical and mental health issues such as weak willpower, lack of vitality, social withdrawal, introversion, anxiety, and depression in physical activities and daily life, [name], the head of the Sports and Health Curriculum Standard Development and Revision Team, along with his research team, conducted long-term theoretical research and practical exploration to create the China Health and Physical Education Curriculum Model. This model, which is the first publicly published physical education curriculum model in China that fully aligns with the "Physical Education and Health Curriculum Standards," has been increasingly adopted by teachers and has benefited more and more students through the establishment of experimental base schools and its widespread promotion.

Metabolomics, a discipline developed after genomics and proteomics, enables a "holistic" scan of metabolites (molecules smaller than 1000 Da) without predefined target indicators, followed by analysis of significant metabolic biomarkers and differences, to observe the overall metabolic status of the body. Metabolites are the final endpoints of upstream biochemical processes and closely reflect the expressed phenotype. Exercise often induces changes in body metabolism, such as glucose metabolism, amino acid metabolism, and lipid metabolism, leading to alterations in the quantity or quality of small molecules in the body. These changes in metabolites provide a theoretical basis for selecting appropriate exercise intensity in exercise prescriptions. High-throughput metabolomics data based on mass spectrometry are helpful for constructing the body's overall metabolic network and discovering metabolic targets. Advances in mass spectrometry technology have facilitated research into the body's response to acute or chronic exercise loads at the metabolic level. Urine, an important medium for metabolism in the body, is the main carrier of metabolic products and has the advantage of being non-invasive when obtaining metabolomic samples, offering clear advantages.

The human body is an organic system, and exercise training, as an intervention, can have broad and profound effects on the body. By utilizing metabolomics concepts and techniques, it is possible to identify differential metabolites before and after exercise intervention and analyze the metabolic pathways involved. This allows for the observation of changes in metabolites during training, providing insights into the molecular mechanisms through which exercise promotes health and supporting the scientific formulation of exercise prescriptions. However, research on exercise metabolomics in China is still in its early stages, with very few reports on the application of metabolomics in school sports.

Previous studies have shown that physical education teaching under the China Health and Physical Education Curriculum Model can effectively improve students' physical and mental health, with results significantly better than traditional physical education teaching. However, there have been no reports on the internal mechanisms of the China Health and Physical Education Curriculum Model in promoting students' physical and mental health. This study will employ the China Health and Physical Education Curriculum Model for 12 weeks of physical education instruction. Before and after the teaching, relevant physical and psychological health indicators will be tested. Using non-targeted metabolomics technology, changes in metabolites before and after teaching will be detected, and the improvement effects and mechanisms of both one-time and long-term teaching using this model on students' physical and mental health will be analyzed. The goal is to provide new insights into improving students' physical and mental health through the China Health and Physical Education Curriculum Model.

**2. Research Objective**

This study will use the China Health and Physical Education Curriculum Model for 12 weeks of physical education teaching. Relevant physical health and psychological health indicators will be tested before and after the teaching. Changes in metabolites before and after the teaching will be detected through non-targeted metabolomics technology. The study will analyze the effects and metabolic mechanisms of one-time and long-term teaching using the China Health and Physical Education Curriculum Model on improving students' physical and mental health levels, aiming to provide new insights into improving students' physical and mental health through this model.

1. **Research Methodology**

- 1. Participants and Grouping

The sample size was calculated using G*Power software, selecting “Means: Difference between two independent means (two groups)” under “t tests.” The assumptions included a medium effect size of 0.5, an α error probability of 0.05, and a power (1 - β error probability) of 0.80, with equal sample sizes in both groups. The minimum required sample size for the study was calculated to be 64.

This study employed a randomized controlled trial design. Six classes of the same grade were randomly selected, with three assigned to the experimental group and the other three to the control group. The researchers wrote the allocation information for each participating class (e.g., experimental or control group) on slips of paper and placed these slips into envelopes. Each envelope contained the random allocation information for the respective class. Both the participants and their parents in the two groups were introduced to the content of the experiment and the precautions during the experimental process to ensure they had a detailed understanding. After obtaining the opinions of the student participants and their parents based on the inclusion and exclusion criteria, informed consent forms were signed.

3.2 Inclusion Criteria, Exclusion Criteria, Criteria for Removal, and Mid-study Withdrawal Criteria

Inclusion criteria: (1) Primary and secondary school students; (2) Able to complete the 12-week intervention and the three tests before the intervention, after the first intervention, and after 12 weeks of intervention.

Exclusion criteria: (1) Students with contraindications to physical activity; (2) Students with severe cardiovascular or musculoskeletal diseases; (3) Students who are sick, injured, have chronic diseases, are taking medication, or are in their menstrual period (female students); (4) Students who have not signed the informed consent form.

Criteria for removal: (1) Students absent for more than one-third of the sessions; (2) Students who are unable to complete the tests due to personal or family reasons; (3) Students who participated in other sports training sessions during the intervention, violating the intervention plan.

Mid-study withdrawal criteria: Students who transferred schools or could not continue participating in the study due to other reasons.

3.3Experiment Content

This study was primarily conducted in primary and secondary schools, involving six classes (approximately 300 students) who voluntarily participated. Three classes were designated as experimental groups, which adopted the Healthy Physical Education Curriculum Model of China for physical education instruction, while the other three classes served as control groups, receiving traditional physical education instruction.

The experimental groups underwent 12 weeks of physical education instruction based on the Healthy Physical Education Curriculum Model of China, whereas the control groups followed the conventional traditional physical education instruction for the same duration. Pre- and post-instruction assessments were conducted to measure the students' physical and mental health indicators. The physical health indicators were evaluated according to the National Student Physical Health Standard (Revised in 2014), which included anthropometric measurements, vital capacity, speed, strength, flexibility, agility, and other indicators. The mental health indicators were assessed through questionnaires, covering healthy behaviors, sportsmanship, depressive symptoms, and other indicators. Additionally, 40 students (20 from the experimental group and 20 from the control group) were randomly selected to provide 15 ml of urine samples before instruction, after the first session of instruction, and after 12 weeks of instruction. Non-targeted metabolomics techniques were employed to detect changes in metabolites within the body, in order to explore the underlying mechanisms by which exercise promotes health.

Furthermore, during the instructional period, all students in both groups were required to wear Polar heart rate monitors to track their exercise heart rates. Questionnaires were also used to assess extracurricular physical activity, diet, and sleep patterns, in order to eliminate metabolic interferences resulting from other factors.

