3.5 Experimental Procedure

Informing the research process and precautions—Grouping by class—Pre-instruction testing (including physical health indicators, mental health indicators, and metabolite collection)—Testing after the first session of instruction (metabolite collection only)—Conducting 12 weeks of physical education instruction (experimental groups adopting the Chinese Healthy Physical Education Curriculum Model, control groups adopting traditional physical education instruction)—Post-instruction testing (consistent with pre-instruction testing).

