3.8 Metabolomics Method

Forty students were randomly selected (20 from the experimental group and 20 from the control group). Urine samples (15 ml) were collected from these students before instruction, after the first session of instruction, and after 12 weeks of instruction. The samples were processed and analyzed using non-targeted metabolomics based on liquid chromatography–mass spectrometry (LC-MS) to identify differential metabolites before and after a single session of instruction, as well as before and after long-term instruction. Metabolic pathway analysis was also conducted to obtain metabolic fingerprints before and after the intervention.

Principal component analysis (PCA) and orthogonal partial least squares discriminant analysis (OPLS-DA) were employed to elucidate the differences in metabolic profiles before and after the intervention. Differential metabolites were further screened using t-tests of intragroup mean metabolite concentrations, OPLS-DA, and clustering analysis. The mass-to-charge ratios (m/z) of the metabolites were matched and analyzed against the Human Metabolome Database and the Kyoto Encyclopedia of Genes and Genomes (KEGG) database for structural identification, enrichment, and topological analysis of the differential metabolites. This approach was used to explore the metabolic pathways involved in the differential metabolites before and after a single session of instruction, as well as before and after long-term instruction, under the Healthy Physical Education Curriculum Model of China.

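### The one-time health aim cannot be answered because no health indicator is measured after the first lesson, and the stated 12-week analyses do not link metabolite change to health change

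*Protocol*

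**What the plan says.** The objective in Protocol section 2 reads "The study will analyze the effects and metabolic mechanisms of one-time and long-term teaching", directed at better physical and mental health. Section 1 presents the unreported internal mechanism as the gap the trial fills.

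The measurements are:
- **Health indicators** (section 3.3): "Pre- and post-instruction assessments were conducted to measure the students' physical and mental health indicators".
- **Urine** (section 3.3): "40 students (20 from the experimental group and 20 from the control group) were randomly selected" to give samples before instruction, after the first lesson and after 12 weeks, "in order to explore the underlying mechanisms by which exercise promotes health".
- **First-lesson test** (section 3.5): "Testing after the first session of instruction (metabolite collection only", so nothing else is recorded at that point.

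The stated analyses are:
- **Metabolites** (section 3.8): PCA and OPLS-DA "were employed to elucidate the differences in metabolic profiles before and after the intervention". Then: "Differential metabolites were further screened using t-tests of intragroup mean metabolite concentrations, OPLS-DA, and clustering analysis". Database matching and pathway analysis follow, for the single lesson and for the long term.
- **Health indicators** (section 3.10): paired t-tests within group, and independent t-tests between groups at baseline and on the change.

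**The concern.** An effect of one lesson on health, and a mechanism for it, needs a health measurement after that lesson. None is scheduled.

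A mechanism for a 12-week effect needs, at the least, evidence that students whose metabolites changed more also changed more in health. The two described analyses never meet: no health variable enters section 3.8 and no metabolite enters section 3.10. Both could be positive and still show only that metabolism and health each changed over a period of teaching. The mechanism is the trial's stated novelty, so the gap touches its main claim.

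**Working it through.** **The plan's own figure.** Section 2 gives a minimum sample of 64 for two independent means (effect size 0.5, alpha 0.05, power 0.80). A noncentral-t calculation at two-sided 0.05 gives 64 per group, 128 in total, with power 0.801. The figure reproduces as a per-group number. It sizes a comparison of group means, not the metabolomics subset, and has no further bearing here. The protocol gives no calculation for the 40 donors.

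**What is measured when** (sections 3.3 and 3.5):

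| Time | Urine (40 donors) | Health indicators |
| --- | --- | --- |
| Before instruction | yes | yes |
| After first lesson | yes | no |
| After 12 weeks | yes | yes (section 4.2 lists physical only) |

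- *One-time teaching.* The health change from baseline to the first-lesson test does not exist as a variable. No t-test, correlation or mediation model can be computed on it.
- *12-week teaching.* Both changes should exist for the same 40 students, so a link is possible but not described.
- *Mental health.* Section 3.5 makes the final test the same as the first, which includes mental indicators. Section 4.2 names mental indicators before the intervention, but only physical indicators and urine after it.

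**What a link in the 40 donors could detect.** By the Fisher z approximation, the smallest correlation detectable with 80% power is r = tanh((z_alpha + z_beta)/sqrt(n − 3)). One two-sided test at 0.05 has z_alpha + z_beta = 1.960 + 0.842 = 2.802.

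- n = 40: tanh(2.802/sqrt(37)) = tanh(0.461) = 0.43.
- n = 20 (one arm): tanh(2.802/sqrt(17)) = tanh(0.680) = 0.59.
- n = 40, adjusted for arm (one more degree of freedom): tanh(2.802/sqrt(36)) = tanh(0.467) = 0.44.

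With several tests, alpha is divided by the number of tests (Bonferroni). The protocol gives no number of tests, so these are assumptions:

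| Tests assumed | Detectable r, n = 40 | Detectable r, n = 20 |
| --- | --- | --- |
| 1 | 0.43 | 0.59 |
| 20 | 0.56 | 0.73 |
| 100 | 0.61 | 0.78 |
| 1000 | 0.67 | 0.83 |

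For a true r of 0.3 and a single test, power is 0.47 with 40 students and 0.25 with 20. About 85 students would be needed for 80%: (2.802/0.3095)² + 3 = 84.95. All these figures treat students as independent, although they come from six classes.

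**The case against.** A reader might infer that the design never connects metabolites with health, so that no mechanism could ever be concluded and any pathway that shifts would be reported as one. The documents do not support this for the 12-week part. The donors are trial students with planned measurements of both kinds, so the gap lies in the stated analysis, not in data collection. A statistical analysis plan, not shown here, could add the link. The protocol also sets no rule for declaring a mechanism. Its wording is often softer: section 1 speaks of insights, section 3.3 of exploring mechanisms, and section 3.8 says "This approach was used to explore the metabolic pathways involved in the differential metabolites before and after a single session of instruction". These points stand, and they reduce the 12-week part to a mismatch between the objective and the analyses described.

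One could also argue that any pathway common to all physical education lessons would show up in the 20 control donors. That is possible, but section 3.8 names only intragroup t-tests. Comparing arms is a separate question, which a metabolite–health correlation does not settle.

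A further objection is that the one-time part has data after all, namely heart rate during lessons (section 3.3), or the acute metabolite response related to health at week 12. Heart rate is recorded there to track exercise and is not among the health indicators of sections 3.6 and 3.7. The week-12 change follows 36 lessons, not one. Neither supplies a health effect of one-time teaching, and no analysis plan can repair this.

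Finally, a correlation in 40 students shows association, not mechanism. That is correct, and it is why the aim needs rewording whether or not the analysis is added.

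**Conclusion.** The point holds in two parts of unequal strength. For one-time teaching, the objective in section 2 and the schedule in section 3.5 do not fit together, and the health aim cannot be answered. This rests on the schedule alone. For 12-week teaching, the analyses described support a statement about metabolic changes accompanying the teaching and no more. That holds as far as the protocol's text goes.

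A link added in the 40 donors could show only fairly strong associations: r of about 0.43 for one test, or 0.56 to 0.67 across an assumed 20 to 1000 tests. These values assume complete data on all 40, 80% power, two-sided 0.05 and no clustering by class. Any link to mental health depends on those indicators being measured after the intervention, on which sections 3.5 and 4.2 differ. The change is worth making: it costs little and alters what the trial may conclude.

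**What to change.** 1. **Section 2.** Restrict the one-time aim to describing the acute metabolic response. Reword the long-term aim as metabolic changes accompanying the teaching and their association with change in health indicators.
2. **Section 3.8.** Add an exploratory analysis in the 40 donors. Relate the baseline-to-week-12 change in a small number of metabolites or pathway scores to the change in a few health indicators named beforehand, adjusted for arm. Because the method is untargeted, fix the rule for choosing the metabolites or scores before the health data are examined. Standardise sex-specific tests within sex: the endurance run is 800 m for girls and 1000 m for boys, and the strength test also differs, so raw results are not on one scale. Report confidence intervals, acknowledge multiplicity and clustering by class, and state that the result is association, not mechanism.
3. **Sections 3.5 and 4.2.** Reconcile whether mental health indicators are measured after the intervention.

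The cost is a few lines of text and one small analysis of data already planned, with no added burden on the students. The downside is a more modest stated conclusion.

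### The stated aim includes the effect of one-time teaching on physical and mental health, but no health indicator is measured after the first lesson, so that part of the aim cannot be estimated

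*Protocol*

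**What the plan says.** The aim appears twice in the Protocol. Section 2 (Research Objective) reads "The study will analyze the effects and metabolic mechanisms of one-time and long-term teaching using the China Health and Physical Education Curriculum Model" and continues "on improving students' physical and mental health levels, aiming to provide new insights". Section 1 (Background) is more explicit: "the improvement effects and mechanisms of both one-time and long-term teaching using this model on students' physical and mental health will be analyzed". Both sentences list effects and mechanisms as separate items, attach both to one-time as well as long-term teaching, and name physical and mental health as what is to improve.

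The schedule is in section 3.5 (Experimental Procedure), which has three test occasions:

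- Before teaching: "Pre-instruction testing (including physical health indicators, mental health indicators, and metabolite collection".
- After lesson 1: "Testing after the first session of instruction (metabolite collection only".
- After 12 weeks: "Post-instruction testing (consistent with pre-instruction testing".

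Section 3.3 (Experiment Content) agrees: "Pre- and post-instruction assessments were conducted to measure the students' physical and mental health indicators". It takes urine on three occasions from 40 randomly chosen students, 20 per group. Section 3.8 describes the single-lesson analysis in terms of metabolites and pathways only.

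**The concern.** The aim asks whether one lesson improves physical and mental health. The schedule contains no physical or mental health value between baseline and week 12, so that question has no outcome data. This is a conflict between two parts of the same document. No analysis plan can settle it, because no method of analysis can supply a measurement that was not taken.

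What is at stake is interpretation. With the aim worded as it is, the only lesson-1 result available to report against it is a shift in urinary metabolites. A reader of the final report could take that shift as evidence that one 40-minute lesson improved health, although no health indicator was measured at that time to relate it to.

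**Working it through.** The Protocol gives no figure on this point, and its sample-size calculation plays no part in it. The check sets the aim beside the measurement schedule.

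**Step 1. Split the aim into its parts.** Sections 1 and 2 name two kinds of result (effects on health, metabolic mechanisms) and two exposures (one-time, long-term): 2 × 2 = 4 parts.

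**Step 2. List what is measured and when** (sections 3.3, 3.5 and 3.8).

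| Measure | Before teaching | After lesson 1 | After 12 weeks |
| --- | --- | --- | --- |
| Physical health indicators (section 3.6) | yes | no | yes |
| Mental health indicators (section 3.7) | yes | no | yes |
| Urinary metabolites (20 + 20 students) | yes | yes | yes |

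**Step 3. Match each part to the contrast it needs.**

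| Part of the aim | Contrast needed | Data available? |
| --- | --- | --- |
| Long-term effect on health | week 12 minus baseline, health indicators | yes |
| Long-term metabolic change | week 12 minus baseline, metabolites | yes, 20 + 20 |
| One-time metabolic change | after lesson 1 minus baseline, metabolites | yes, 20 + 20 |
| One-time effect on health | after lesson 1 minus baseline, health indicators | no; the later value is never taken |

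One part of four cannot be estimated. The obstacle is a missing measurement and not a shortage of students, so enlarging the trial or the urine subsample would not help.

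**Step 4. Look for any other text that supplies the missing value.**

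- The inclusion criteria in section 3.2 require students to complete three tests, one of them after the first lesson. Section 3.5 makes that middle test urine only.
- Section 3.3 has all students wear heart rate monitors during teaching. This records exercise load during lessons. Heart rate is not among the physical health indicators in section 3.6.
- Section 3.10 compares values before and after the intervention and mentions no analysis of health indicators after lesson 1.
- The timeline in section 4.2 lists pre- and post-intervention data collection and no health test in between. Its post-intervention list does not mention mental health, but the list is not exhaustive, and sections 3.3 and 3.5 both place mental health after teaching, so the long-term part is taken as covered.

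None of these supplies a health value after lesson 1.

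**Step 5. Check what the one-time metabolite data can show.** The t-tests named in section 3.8 are of within-group means, and its other methods are described for differences before and after teaching. The between-group test in section 3.10 concerns the change from before to after the intervention. As written, then, the lesson-1 analysis describes how metabolites change within a group after one lesson. It does not separate the curriculum model from a traditional lesson, although the control students' urine needed for that is collected.

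**The case against.** The strongest reply is that the intent is plain from the operational sections. Section 3.8 frames the single-lesson question as one about metabolites and pathways. The Background sentence opens by naming untargeted metabolomics as its tool. Section 3.5 states the urine-only restriction openly. Anyone following sections 3.3 to 3.8 would collect the intended data, and no long-term estimate, test or sample size is affected. On this view the defect is loose wording of an aim.

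Much of that stands. It explains what the sponsor probably meant, and it keeps the remedy small. It does not remove the conflict, because sections 1 and 2 list effects apart from mechanisms and attach both to one-time teaching. If only the acute metabolic response was meant, the aim should say so. Nor can metabolites stand in for the health indicators: the Background says that metabolites closely reflect phenotype, but the Protocol specifies no link from any metabolite to any health indicator, and at lesson 1 there is no indicator to link to.

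Three stronger readings are tempting, and the document does not support them.

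- A reader might infer that the whole one-time aim, and so half of the objective, lacks data. It does not: the one-time metabolite change is measured in 20 + 20 students.
- A reader might infer that only the 40 urine donors have any data from the first lesson. Heart rate is monitored in all students during teaching, and the share who give urine is beside the point: the gap would be the same if all of the roughly 300 did.
- A reader might infer that the trial will report a metabolite shift as a health benefit. The Protocol states an aim and commits to no such conclusion. The risk lies in how the wording may be used later.

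**Conclusion.** The point holds for one part of the aim. The effect of one-time teaching on physical and mental health is promised in sections 1 and 2 and cannot be estimated from the schedule in sections 3.3 and 3.5, in either group and at any sample size. The other three parts (one-time metabolite change, long-term metabolite change, long-term health effect) have data.

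This rests on two readings. The first is that effects in sections 1 and 2 means effects on physical and mental health, which is what both sentences say. The second is that section 3.5 governs what is collected after lesson 1, which section 3.3 supports. The consequence is confined to what the trial may conclude about a single lesson; the long-term comparison is untouched.

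**What to change.** In sections 1 and 2, restate the aim in two parts:

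- One-time teaching: the acute change in urinary metabolites from before to after lesson 1, in the 40-student subsample.
- Long-term teaching: physical health, mental health and urinary metabolites, from baseline to week 12.

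Add that no conclusion will be drawn about one-time improvement in physical or mental health. This is a change of wording. It needs no new data and can be made even after data collection.

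If the acute metabolite change is to be attributed to the curriculum model, section 3.8 should also compare the change from before to after lesson 1 between the experimental and control students. The control urine is already in the schedule, so the cost is a small added analysis, but it goes beyond wording. If the sponsor does not want that comparison, the lesson-1 result should be described as a within-group change only.

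The downside is a narrower claim.

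### The stated minimum of 64 for the study is the per-group figure (128 in total), and the 80% power behind it assumes individually allocated students, not six allocated classes

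*Protocol*

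**What the plan says.** The paragraph on participants and grouping, at the start of the Research Methodology part of the protocol, describes a G*Power calculation for a t test of two independent means. Its inputs are "a medium effect size of 0.5, an α error probability of 0.05, and a power (1 - β error probability) of 0.80". The two arms are taken to be of the same size. The result is given as: "The minimum required sample size for the study was calculated to be 64". Whether the test is one-sided or two-sided is not stated.

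The next paragraph allocates whole classes, three to each arm, with one envelope per class. Section 3.3 gives the planned size: "involving six classes (approximately 300 students) who voluntarily participated". Section 3.10 compares the arms with independent-sample t tests, applied to baseline values and to pre-to-post differences, and names no class term. The protocol gives no intraclass correlation or design effect.

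**The concern.** There are two separate problems in one paragraph.

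- **The label.** For these inputs 64 is the familiar two-sided number per group, yet the sentence presents it as the number for the whole study. Anyone using 64 to judge whether enough students remain after the removals and withdrawals allowed in section 3.2 would be using half the correct figure.
- **The design.** The calculation treats each student as an independent unit. Students taught together in one class share a teacher, a timetable and a peer group, so their outcomes may be correlated, and there are only three allocated units per arm. The 0.80 entered in the calculation therefore does not describe the trial being run. The same assumption carries into the planned between-group test, where it affects the false-positive rate.

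**Working it through.** **Inputs.** From the protocol: d = 0.5, α = 0.05, power 0.80, equal groups, six classes (three per arm), about 300 students. Derived: 300 / 6 = 50 students per class and 150 per arm. Assumed, because the protocol gives no value: an ICC of 0.01 to 0.10, equal class sizes, and d in units of the total student SD of the outcome analysed.

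**1. The protocol's own figure.** With n per group, the noncentrality is d × √(n/2) on 2n − 2 degrees of freedom.

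- Two-sided: n = 63 gives power 0.795. n = 64 gives noncentrality 0.5 × √32 = 2.83 and power 0.801. The requirement is 64 per group, 128 in total.
- One-sided: n = 50 gives 0.799 and n = 51 gives 0.806. The requirement is 51 per group, 102 in total.

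Neither reading gives 64 in total. The number 64 matches only the two-sided per-group result.

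**2. A study of 64 students.** With 32 per group, the noncentrality is 0.5 × √16 = 2.00. Two-sided power is 0.504 (one-sided 0.631). Two-sided power of 80% is reached only at d = 0.71.

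**3. The six-class design, analysed by class.** The design effect is DE = 1 + (50 − 1) × ICC. The standard error of the difference, in SD units, is SE = √(2 × DE / 150). The noncentrality is 0.5 / SE on 6 − 2 = 4 degrees of freedom, with a two-sided critical value of 2.776. Power of 80% needs a noncentrality of 3.76, so the detectable effect is 3.76 × SE.

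| Assumed ICC | DE | SE | 0.5 / SE | Power at d = 0.5 | Effect detectable at 80% |
|---|---|---|---|---|---|
| 0 | 1.00 | 0.115 | 4.33 | 0.89 | 0.43 |
| 0.01 | 1.49 | 0.141 | 3.55 | 0.76 | 0.53 |
| 0.05 | 3.45 | 0.215 | 2.33 | 0.43 | 0.81 |
| 0.10 | 5.90 | 0.280 | 1.78 | 0.28 | 1.05 |

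Setting 0.5 / SE = 3.76 and solving gives ICC ≈ 0.007. Above that, power is below 0.80.

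**4. Sensitivity to the degrees of freedom.** A normal approximation that ignores the 4 degrees of freedom gives power of 0.94, 0.65 and 0.43 at ICC 0.01, 0.05 and 0.10. It crosses 0.80 at an ICC of about 0.028.

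**5. The student-level t test as written.** This test uses SE = √(2/150) = 0.115 whatever the ICC. Its actual two-sided type I error is about 2 × [1 − Φ(1.96 / √DE)]:

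- ICC 0.01: 1.96 / √1.49 = 1.61, giving 0.11
- ICC 0.05: 1.96 / √3.45 = 1.06, giving 0.29
- ICC 0.10: 1.96 / √5.90 = 0.81, giving 0.42

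**The case against.** **The planned enrolment makes the slip harmless.** About 300 students is more than twice 128, and nowhere does the protocol use 64 as a recruitment target, stopping point or retention floor. Falling to 64 would mean losing 236 of 300 students, about 79%. This stands as regards consequence: a reader might infer from the wrong total that the trial is short of students or has only an even chance of detecting its target effect, and the documents do not support that. It does not make the sentence correct, and it does not answer the clustering point, where the limit is the number of classes.

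**The 0.80 is an input, not a claim about 300 students in six classes.** This also stands. As an input it is right for 64 per group with individual allocation. The fair criticism is that the calculation describes a different allocation unit from the trial's, and no other power statement is offered.

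**The class-level powers belong to an analysis the protocol does not plan.** Correct, and it changes the direction of the main risk. A reader might infer that the chief danger is a null result misread as no effect. Under section 3.10 as written, the test understates its standard error whenever the ICC is positive, so the chief danger is a false positive. The low powers apply once the analysis accounts for class.

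**The ICC is unknown.** True. The protocol also does not say whether d = 0.5 refers to post-test values or to pre-to-post differences, so the relevant ICC could be that of change scores. That is why a range is shown. The 0.007 threshold depends on counting only 4 degrees of freedom, which is the more defensible choice with six classes. The looser threshold is 0.028.

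**Conclusion.** The point holds in two parts of different weight.

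The total is wrong as written. On the protocol's own inputs the requirement is 64 per group, 128 in total (102 if one-sided), and this needs no outside assumption. Because about 300 students are planned, the error by itself leaves no shortfall.

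The mismatch with class allocation matters more. The 80% does not carry over to three classes against three. Under an analysis that respects the classes, power at d = 0.5 runs from about 0.76 to 0.28 over ICCs of 0.01 to 0.10. Under the student-level test as written, type I error runs from about 0.11 to 0.42 over the same range. These sizes rest on the assumed ICCs and on equal classes of about 50. That the calculation and the between-group test both omit class does not depend on those assumptions.

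**What to change.** 1. In the sample-size paragraph, state the result as 64 per group, 128 in total, assuming individual randomisation, and say that the test is two-sided.
2. Replace the unqualified 80% with the power, or the detectable effect, of the six-class design over a stated ICC range such as 0.01 to 0.10. Say that these figures apply to an analysis that accounts for class, and name the outcome scale to which d = 0.5 refers.
3. Bring section 3.10 into line by replacing the student-level between-group t test with an analysis that accounts for class and its few degrees of freedom, for example a t test on class means with 4 degrees of freedom. Steps 2 and 3 belong together: without step 3, the sample-size paragraph would give the power of an analysis the protocol does not perform.

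The cost is a paragraph of wording, a matching change to section 3.10, and a less favourable stated power. The correction itself calls for no extra enrolment.
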